**Fig. 1 Fig1:**
[figure not shown]
Study flowchart

The sample size calculation is based on the primary outcome measure ‘frequency of nighttime awakenings’, as nighttime awakenings are expected to decrease due to the program and are clinically relevant in improving healthy infant sleep. The effect size is expected to be small to medium (Cohen’s *d* of 0.3). T3 (9 months) is chosen as the main reference timepoint for the primary analysis, as this is the timepoint at which both preventive and behavioural strategies from the program could have been used by parents. Using a conservative estimate based on a one-sided independent samples T-test for two groups, with T3 as the main reference timepoint of the primary analysis, an alpha of 0.05 and a power of 0.80 the total sample size is 278. Assuming a dropout of about 9% the estimated total sample size becomes 306. In addition, to control for potential clustering effects at the level of YHC teams, given an estimated intra-cluster correlation coefficient of about 0.02 and an average cluster size of 4, the total sample size required is 324, with 162 participants in the program group and 162 participants in the control group.

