### Data collection

#### Primary outcome

The primary outcome of this study is sleep quality of 0-2-year-old infants and will be assessed with a sleep diary filled out by parents, measuring the number and duration of daytime naps, bedtime, time to sleep onset, the number and duration of nighttime awakenings and the time the child gets out of bed in the morning. Parents are asked to fill in the diary for four consecutive days [62]. Sleep quality will be assessed when the infant is 10 weeks, 6 months, 9 months, 14 months and 24 months old. The sleep diary was developed for this study and can be filled in digitally or on paper. All study outcomes, assessment moments and instruments are listed in Fig. 2.

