### Data analysis

Continuous variables will be described in terms of means and standard deviations, while categorical data will be described using percentages and frequencies. Possible demographic differences between the program group and control group will be analysed using independent samples T-tests for continuous outcome variables and Pearson chi-square tests for categorical variables. The primary outcome ‘frequency of nighttime awakenings’ will be analysed by comparing the program group with the control group using a linear mixed model to account for potential confounders or relevant covariates, as well as possible clustering effects at the level of YHC teams, with T3 being the main timepoint of focus of the analysis. In case no substantial clustering effects are found, alternative approaches will be used to analyse the data at T3 if appropriate (e.g. linear regression or a one-sided independent samples T-test).

When appropriate, relevant covariates will be included into the analysis, such as feeding problems and major life events (e.g. parental divorce or illness at the moment of assessment), within a multiple regression analysis framework. In addition to the main analysis, further exploratory analyses will be performed. These include: effectiveness analyses at other assessment times, a repeated measurements analysis to identify changes between groups over the follow-up and analysis of program effects on secondary outcome measures, using the same approach as for the primary outcome in case of continuous variables and logistic regression or chi-square tests in case of categorical variables. All analyses will be performed in IBM SPSS Statistics 27 and/or R. Regarding the process evaluation, quantitative data will be analysed using descriptive statistics. The data of the highly structured part of the qualitative interviews will be reported in frequencies and percentages. The data of the in-depth part of the qualitative interviews will be transcribed verbatim and used as input for the iterative co-creation process and to provide context to the data from the highly structured part.

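### The primary night-awakenings comparison is described as a 9-month analysis with the repeated-measures model left exploratory, so earlier diaries do not protect it against group-dependent dropout

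*Protocol article*

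**What the plan says.** The Data analysis section of the protocol article assigns the primary outcome, frequency of night awakenings, to a linear mixed model "with T3 being the main timepoint of focus of the analysis". The reasons given for that model are confounders or covariates and possible clustering at the level of Youth Health Care teams. Correlation between diaries of the same infant is not among them. If clustering turns out not to be substantial, the section allows linear regression or a one-sided t-test on the T3 data. The Abstract says the same: mixed model if the data are clustered, otherwise a t-test or regression.

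The section then lists further analyses that it calls exploratory. Among them is "a repeated measurements analysis to identify changes between groups over the follow-up".

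Under Primary outcome, the diary schedule is: "Sleep quality will be assessed when the infant is 10 weeks, 6 months, 9 months, 14 months and 24 months old". Two diaries therefore come before T3 and two after it.

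The sample-size paragraph (Participants section, after Fig. 1) sizes the study for a two-group comparison at T3 and adds an allowance for loss: "Assuming a dropout of about 9% the estimated total sample size becomes 306".

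**The concern.** A comparison that uses one time point rests on the parents who supply a diary at that time. If the parents lost before 9 months differ from those retained in how their infants slept earlier, and if that selection differs between program and control groups, the T3 contrast is shifted by something other than the program.

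Several features make such selection plausible. Study setting states that allocation was not random and that researchers, parents and professionals were not blinded. The outcome is a four-day diary kept by the parent. The Background links infant sleep problems to parental fatigue, which could affect whether a diary is completed. The direction cannot be known in advance. Losing poor sleepers mainly from the program group would flatter the program, and losing them mainly from the control group would hide an effect.

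The plan collects the 10-week and 6-month diaries and already intends to fit a model that can use them. It places that model outside the primary analysis.

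**Working it through.** **1. The plan's sample size reproduces.** The inputs come from the sample-size paragraph: d = 0.3, one-sided t-test, "an alpha of 0.05 and a power of 0.80 the total sample size is 278", 9% dropout, intra-cluster correlation 0.02, mean cluster size 4.
- The t-test solution is 138.07 per arm, rounded up to 139, so 2 × 139 = 278.
- Dropout: 278 / (1 − 0.09) = 305.5, so 306.
- Design effect: 1 + (4 − 1) × 0.02 = 1.06, and 306 × 1.06 = 324.4, stated as 324.

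Dividing by 0.91 credits a parent lost before T3 with no information. That fits a T3-only primary analysis.

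**2. Which analysis is described.** Three statements bear on this.
- The mixed model's stated purposes are covariates and team clustering.
- It may be replaced by a t-test or regression when team clustering is negligible. In a model holding several diaries per infant, within-infant correlation would remain without team clustering, so that replacement would not follow.
- The repeated-measures analysis is named separately, as exploratory.

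Together they describe a cross-sectional comparison at T3.

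**3. Power.** At 9% dropout, 324 × 0.91 = 294.8 parents have T3 data and about 29 do not. Allowing for clustering, 294.8 / 1.06 = 278.2, which gives 80.3% power.

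For a model that also uses the two earlier diaries, effective N = N(1 − d) / (1 − R²d), where d here is the dropout fraction and R² = 2r² / (1 + r). This assumes equal correlation r between ages and both early diaries present for every parent lost. The documents give no r.

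| Assumed r | R² | Effective N at T3 | Power |
|---|---|---|---|
| 0.3 | 0.138 | 298.6 | 80.7% |
| 0.5 | 0.333 | 304.0 | 81.3% |
| 0.7 | 0.576 | 311.0 | 82.1% |

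The gain is 0.4 to 1.8 percentage points, so precision is not the argument.

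**4. Bias under assumed dropout.** Let Z be standardised 6-month awakenings. Suppose that in one arm the log-odds of loss rise by b per SD of Z, and that in the other arm loss is unrelated to Z. The retained parents' mean of Z in the affected arm shifts by −E[Z·p(Z)] / (1 − p̄), where p(Z) is the probability of loss and p̄ its mean. The T3 contrast is biased by r times that shift.
- b = 1, p̄ = 0.09: E[Z·p(Z)] = 0.0748 by numerical integration, and 0.0748 / 0.91 = 0.082. Multiplying by r = 0.3, 0.5, 0.7 gives 0.025, 0.041, 0.058 SD.
- Simulation of the same scenario (3000 trials per setting, 162 per arm, about 9% dropout) gave 0.03 to 0.07 SD, with 0.044 at r = 0.5. This is 10% to 23% of d = 0.3. The two methods agree to about 0.01 SD.
- b = 0.5, p̄ = 0.09: 0.0401 / 0.91 = 0.044, so 0.013 to 0.031 SD. Simulation gave 0.01 to 0.03.
- Same dependence and same dropout in both arms: the shifts cancel. Simulation gave less than 0.001 SD.
- b = 1 with about 21% dropout, more than twice the planned rate: simulation gave 0.06 to 0.14 SD.

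For scale, the standard error of the T3-only estimate in simulation was 0.117 SD, so 0.044 is 0.044 / 0.117 = 0.38 of a standard error. An estimate using the 6-month value was within 0.005 of zero bias in every b = 1 one-arm setting, with an equal or smaller standard error. That holds because loss was made to depend only on observed 6-month sleep.

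**The case against.** The strongest reply is that the article does not literally restrict the mixed model to T3 records. It calls T3 the main time point of focus, and only the fallback is worded as an analysis of T3 data. A reader might infer that parents lost before 9 months are dropped. The article never says so, and handling of missing diaries is commonly left to a full protocol or analysis plan that is not shown. Imputation from the earlier diaries would be compatible with a T3 primary analysis and would address the same bias. This stands, so the point cannot rest on silence about missing data. It rests on what is stated: the purposes given for the primary model, the fallback, and the exploratory label on the repeated-measures model.

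A reader might also infer that control parents get no sleep support and so have a clear reason to leave. Study setting contradicts this: control regions give usual care and should follow the national infant sleep guidelines. Nor is a bias of a fifth to a third of the expected effect established. It needs strong dependence in one arm only, and the upper end also needs dropout above twice the planned 9%. No figure in the document supports those slopes.

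Choosing 9 months as the primary age is justified in the sample-size paragraph and is not disputed. Retention is also addressed in the design, through vouchers, monitoring at each time point and reminders. These lower the risk without removing it.

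Finally, the repeated-measures model does not correct loss driven by unobserved 9-month sleep. It helps less for parents lost before 6 months, who have at most one diary. Both limits stand.

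**Conclusion.** The point holds as a matter of analysis choice. As described, the primary estimate is a T3 comparison, and the model that would use the other diaries is expressly exploratory. Loss related to earlier sleep in a group-specific way would bias that estimate, and the primary model as described does nothing to correct it.

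The bias cannot be computed from the documents. Under the assumed one-arm dependence it is about 0.03 to 0.07 SD at the planned dropout, which is modest beside a standard error of about 0.12. With half the dependence it is 0.01 to 0.03 SD, and with equal dependence and equal dropout it is near zero. The planned 324 gives about 80% power at 9% dropout under either analysis. The change is worth making because it is cheap, keeps the 9-month question, loses no precision in the cases examined, and removes bias from loss that depends on observed earlier sleep. The evidence does not show that the trial's result will be wrong without it.

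**What to change.** Make the repeated-measures linear mixed model the primary analysis:
- all available diaries, with group by categorical time;
- the same covariates as planned;
- a within-infant covariance structure, unstructured if it converges, with a simpler structure named in advance if it does not;
- a random effect for team.

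The program-control contrast at 9 months is the single primary estimate. Keep the T3-only model as a sensitivity analysis. If team clustering proves negligible, simplify the team term only and keep the within-infant structure. State explicitly that the 10-week and 6-month diaries enter the primary estimate, and how a missing T3 diary is handled.

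The cost is a somewhat more complex model. No new data are needed, the planned SPSS or R can fit it, and the sample size and primary time point stay as they are. The model assumes that missingness depends only on observed data, and it cannot recover parents who supplied no diary.

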### Secondary outcomes

**Sleep Diary.** Bedtime regularity will be assessed using the bedtime item from the sleep diary. Parental perception of infant sleep quality will be measured with two closed-ended questions integrated in the sleep diary: ‘How well did your child sleep last night?’ and ‘How well did your child sleep today during the day?’ These questions are answered on a five-point Likert scale ranging from very well to very badly. Parental sleep is measured with the question: ‘How did you sleep last night?’ and can be answered on a five-point Likert scale ranging from very well to very badly. Parental behaviour regarding infant sleep management is assessed with two study-developed questions in the sleep diary. The first question focuses on how the parent put the child to bed that night and can be answered with one of the following three answers: ‘awake and not tired’, ‘awake and tired’ and ‘when my child was asleep’. The second questions asks how the child fell asleep that night, and can be answered with one of the following four answers: ‘on his/her own, without a parent in the room’, ‘with a parent present in the room, not attending the child in any way’, ‘with a parent present in the room, attending the child’ or ‘the child fell asleep during feeding’.

**Questionnaires.** The questionnaires of this study can be filled in digitally or on paper. Parental behaviour regarding infant sleep management is assessed with the use of the 11 parental behaviour items from the Brief Infant Sleep Questionnaire (BISQ-R): a validated questionnaire for measurement of infant sleep and related parental behaviours and perceptions [63, 64]. Parental perception of infant sleep and parental self-efficacy regarding infant sleep management are assessed using the three parent perception items and the self-efficacy item from the BISQ-R, respectively.

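### For categorical secondary outcomes the plan allows an unadjusted chi-square test of program effect in a non-randomised study, and names no method that handles team clustering

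*Protocol article*

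**What the plan says.** The Data analysis section of the protocol article assigns methods to the secondary outcomes by variable type. Continuous outcomes are handled "using the same approach as for the primary outcome in case of continuous variables". That approach is a linear mixed model that takes in confounders "as well as possible clustering effects at the level of YHC teams". Categorical outcomes are handled by "logistic regression or chi-square tests in case of categorical variables".

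Two other statements in that section bear on this:
- A general covariate provision: "When appropriate, relevant covariates will be included into the analysis, such as feeding problems and major life events". It places this adjustment in a multiple regression framework and does not restrict it to the primary outcome.
- The status of these analyses: "In addition to the main analysis, further exploratory analyses will be performed". The secondary-outcome analyses are listed among them.

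The Secondary outcomes section describes the items. Two parental-behaviour questions in the diary have three and four answer options; of these, "The first question focuses on how the parent put the child to bed that night". Ratings of child and parent sleep are "answered on a five-point Likert scale ranging from very well to very badly". The questionnaires add four-point knowledge statements, five-point items on how often professionals ask about sleep and on satisfaction with advice, and a closed question on help from outside YHC. On the diary, the Primary outcome section says: "Parents are asked to fill in the diary for four consecutive days".

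The Study setting section states that regions were not assigned at random but chosen for practical reasons and willingness.

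**The concern.** Families in the program and control regions may differ in ways that affect how they settle a child or judge the advice they receive. The plan recognises this for the primary outcome by modelling confounders. For categorical outcomes it offers two methods joined by an unqualified 'or', and one of them, the chi-square test, admits no covariates. A chi-square result could therefore be reported as a program effect when it reflects who lives in, or enrols from, which region.

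Two lesser weaknesses sit in the same sentence. Parents under the same YHC team are clustered whatever the scale of the outcome, yet clustering is mentioned only through the continuous route. A Pearson chi-square test also discards the order of ordered answers and so loses power.

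Parental behaviour and satisfaction with advice belong to the study's stated second aim, and the Discussion relies on intermediary outcomes to help explain any change in infant sleep. That is why the choice of test deserves correction even for exploratory analyses.

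**Working it through.** **The plan's own figures.** The document gives no figure for the categorical outcomes. Its sample size (Participants section) supplies the clustering inputs and reproduces:
- One-sided two-sample t-test, d = 0.3, alpha 0.05, power 0.80: 138.07 per group, rounded up to 139; 2 × 139 = 278.
- Dropout 9%: 278 / 0.91 = 305.5, so 306.
- Design effect 1 + (4 − 1) × 0.02 = 1.06; 306 × 1.06 = 324.4, stated as 324 (162 per group).

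**Confounding.** No arithmetic applies, because the document gives no covariate distributions or associations. Set side by side: allocation was non-random; adjustment is provided for within regression; chi-square is not regression. The covariate provision can reach the logistic option but not the chi-square option.

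**Team clustering ignored.** The actual error of a nominal two-sided 5% test is 2 × [1 − Φ(1.96 / √DE)], where DE is the design effect.
- Plan's inputs, DE = 1.06: 1.96 / 1.0296 = 1.904, giving 5.7%.
- If teams contributed more families (assumption, same correlation of 0.02): 10 per team gives DE = 1 + 9 × 0.02 = 1.18 and 7.1%; 20 per team gives DE = 1 + 19 × 0.02 = 1.38 and 9.5%.

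**Ordering ignored.** Assumptions: a five-category item with control proportions 0.15, 0.35, 0.30, 0.15 and 0.05; proportional odds; 147 per group (162 × 0.91 = 147.4); two-sided 5%; 3,000 simulated trials per row.

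| Odds ratio | Power, Pearson chi-square | Power, rank test | Loss (points) |
|---|---|---|---|
| 1.5 | 30% | 50% | about 19 |
| 1.72 | 51% | 73% | about 22 |
| 2.0 | 74% | 90% | about 16 |

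Losses are taken from unrounded values (30.4 against 49.7; 50.6 against 72.6; 73.7 against 89.6). They apply only to ordered items that are in fact tested by chi-square.

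**Four nights, conditional only.** If each child's four nights were entered as independent rows, DE = 1 + 3ρ, where ρ is the within-child correlation (assumed; not in the document).

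| ρ | DE | Actual error, formula | Actual error, simulation of four binary nights |
|---|---|---|---|
| 0.3 | 1.9 | 15.5% | 16.6% |
| 0.5 | 2.5 | 21.5% | 21.5% |
| 0.7 | 3.1 | 26.6% | 28.0% |

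With one summary per child, this inflation does not arise.

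**The case against.** The strongest reply is that the plan's sentence is broad enough to cover a sound analysis. Several parts of that reply stand.

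- A reader might infer that all these analyses are unadjusted. The document does not support that. Logistic regression is named first and takes covariates, and the covariate provision is general. The confounding point holds for the chi-square option only.
- A reader might infer that the four nights will be pooled as independent rows, with error rates of 16% to 27%. Nothing in the document says so. How nights are combined is a detail that an article may leave to the analysis plan, so those rates are a warning about one possible reading and not a property of the plan.
- A reader might infer that ordered answers must be dichotomised. Ordinal and multinomial models are forms of logistic regression and are not excluded. Nor are the Likert items classed as categorical; treated as continuous, they would follow the primary approach and their order would be used.
- Clustering is minor at the plan's stated inputs. The contrast with continuous outcomes is also not absolute: if no substantial clustering is found, the primary approach may itself fall back to linear regression or a t-test.
- The analyses are labelled exploratory.

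What the reply does not remove is that chi-square is permitted as a test of program effect in a non-randomised comparison, with no statement that the adjusted method takes precedence, and that clustering is not mentioned for categorical outcomes.

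**Conclusion.** The point holds in a limited form. The permitted chi-square test cannot adjust for confounders and ignores any ordering, and neither method named for categorical outcomes is said to account for YHC teams.

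The bias from confounding is real in principle but cannot be sized from the document. The clustering effect is small: 5.0% becomes about 5.7% at the stated correlation and team size, and more only if teams contribute many more families than assumed. The power loss of about 16 to 22 points rests on an assumed answer distribution and on an ordered item being tested by chi-square. The primary outcome, its analysis and the sample size are unaffected. This is a minor improvement worth making because it costs little.

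**What to change.** Amend the one sentence in Data analysis that assigns methods to categorical secondary outcomes:

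- Use chi-square tests for descriptive tables only, not to test program effects.
- Estimate program effects with a covariate-adjusted logistic model: binary, ordinal or multinomial according to the item, with the same confounders as the primary model.
- Account for YHC teams by a random intercept or cluster-robust standard errors.
- For items recorded each diary night, use one summary per child or a child-level random effect.
- State which items are treated as continuous and which as ordered or nominal.

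A random intercept for region is not needed, and with only two program regions its variance could hardly be estimated in that group.

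The cost is a few lines of text and somewhat more analysis work. R, already named in the plan, fits these models. No change to data collection or sample size is required.

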## Discussion

This paper describes the study protocol for the development, effectiveness and process evaluation of a program tailored to Dutch YHC to promote sleep in 0-2-year-old infants. The program has several strengths. By using continuous, iterative co-creation cycles and methods such as qualitative interviews, a discussion session and a service design thinking session, parents and professionals were involved in program development. This way, a program was created that addresses the needs of important stakeholders and is compatible with the daily working practice of Dutch YHC. This is an important addition to the current work on the promotion of healthy infant sleep, by adding to the limited number of studies that specifically focus on sustainable integration of infant sleep health promotion in practice-based settings such as YHC and by being suitable for parents with limited (health) literacy [30, 32, 67, 68].

Another strength is that the program components provide solutions for various issues considered present in YHC sleep education, by providing training to improve YHC professionals’ knowledge and skills, reducing time constraints with early sleep information provided outside of consultations and by developing program components that are comprehensible for a wide range of parents, including parents with limited (health) literacy [27, 34, 43]. Furthermore, with program elements based on evidence-based behaviour change methods and scientific sleep literature, the program has a sound scientific core and is also adaptable to fit different contexts regarding its specific sleep content. This enhances program implementation and sustainability [44, 46, 58, 69].

Regarding the study design, a strength is that in addition to the main reference timepoint at nine months, both short-term and long-term effects are investigated, due to having five measurement moments, starting at the age of 10 weeks and continuing until the child is two years old. Furthermore, not only infant sleep outcomes, but also intermediary and parental outcomes are assessed, which increases the studies’ sensitivity to find effects and aids in exploring factors that could be related to changes in infant sleep [49, 70]. When evaluating programs in real life settings such as YHC, it is also important to gain insight in program reach, adoption, implementation, maintenance and possible working mechanisms [71, 72]. Therefore, a thorough program evaluation is performed by combining a quasi-experimental effect evaluation with a mixed methods process evaluation [49, 71–73].

This study also has some limitations. One limitation may be that the study relies on subjective parental self-report using a sleep diary for the assessment of infant sleep. However, for this study, self-report measures were considered to be the most suitable option, for they are easy to administer, provide real-time insight in infant sleep and are considered less burdensome for the infant and more acceptable for parents in comparison with wearable sleep monitoring devices [74–76].

Another limitation may be the use of a quasi-experimental post-test only design, which may lower the study’s internal validity. However, for evaluation of complex, practice-based, population-level programs, it is necessary to find the right balance between internal validity and external validity [49, 70, 72, 77]. In the YHC context randomization is difficult, for being a program region requires quite some investment from local professionals, which is not possible in all YHC regions at all times. A post-test only design was chosen because in a study with newborn children, a pre-test measurement cannot be performed in the same child. Hence a quasi-experimental, post-test only study design was determined to be the most suitable design for this study, having the best balance between internal and external validity.

In conclusion, the ‘Sleep on number 1’ program combines the needs and wishes of parents and professionals with evidence-based sleep health promotion and behaviour change methods into a program that is tailored to Dutch YHC. A robust evaluation is ensured by combing a quasi-experimental effect evaluation with a mixed methods process evaluation. If effective, this program has the potential to be implemented in and disseminated across YHC regions to sustainably promote healthy infant sleep on a population level [30, 34, 35, 38].

